#### RE-AIM framework

2.6.4

This tool encompasses five dimensions, providing a comprehensive analysis of a health intervention's potential [32]. The Reach dimension indicates the number of potentially eligible participants for the intervention. The Efficacy/Effectiveness dimension quantifies the impact of the intervention, taking into account potential negative and positive effects. Adoption is related to the readiness of organizations and teams to initiate the program. Implementation assesses how well the proposed intervention can be applied to real-world conditions, considering planning, practices, costs, and established goals for execution. Lastly, the Maintenance dimension corresponds to the sustainability of a program over time [75].

Given this, the Reach indicators will include recruitment rates, participant characteristics, and participation rates in both the intervention. Efficacy/Effectiveness will encompass intervention group outcomes, including potential individual and collective benefits from the intervention program, as well as impacts on assessed health performances, adverse event rates, participant acceptability, and adherence. Adoption will incorporate quantitative and qualitative feedback on planning, execution, work environment(s), and team involvement. Implementation will evaluate the intended and actual duration of the intervention, proposed goals, any adaptations, as well as costs and user engagement levels. Maintenance will be assessed by both organizers and participants, considering the potential for sustained execution of the HEP and MEP programs over time.

#### Sustainability

2.6.5

After the study execution, assessments and improvements will be made for the continuation of the intervention in the medium and long term, based on the RE-AIM model. This model provides a set of indicators capable of evaluating sustainability, directly related to SDG 3, which advocates for the promotion of health and well-being in populations. Aspects related to the internal and external validity of the intervention program will be considered, evaluated through overall intervention results and focus groups [76]. In this way, we hope for the continued application of these intervention models in other realities in Brazil and other countries, such as Portugal and Mozambique, considering the partners involved in the EISI-SP.

Furthermore, certain parameters, such as adherence based on the participants' gender, related to SDG 10 (reduction of inequalities); the importance of the exercise program for building healthier and more active cities (SDG 11); the use of sustainable practices for intervention program implementation (SDG 13), and the establishment of partnerships and collaborations with local organizations for its implementation (SDG), will be considered and verified, aiming to align with the main UN SDGs related to this type of intervention [35].

#### Barriers and facilitators

2.6.6

In order to evaluate the facilitators and barriers to participation in the exercise program, a focus group will be conducted with the participants. This approach will allow for a more holistic and contextual understanding of the underlying issues that may impact adherence to the EISI-SP, as well as identify social, environmental, and psychological factors that can positively influence or hinder the incorporation of physical activity into their daily lives.

Following methods described in previous studies [77], sessions will be organized with small groups of participants, and a facilitator will lead the discussion, encouraging participants to express their opinions, ideas, experiences, and perceptions regarding their participation in the EISI-SP. The environment will promote interaction among participants, enabling the emergence of new ideas and collective insights on the subject. The information collected during the focus group will be qualitatively analyzed to identify patterns, trends, and relevant issues related to participation in the EISI-SP.

### Focus group analysis

2.7

The focus group will be the qualitative approach used to evaluate the elderly and their participation in EISI-SP. The steps include planning, participant selection, script preparation, session facilitation, discussion and interaction among participants, data recording and analysis [78]. The incorporation of this methodology will provide detailed insights into the perspectives, challenges, and successes of the elderly in the program, assisting in improvements and adaptations to meet their real needs.

### Pilot study

2.8

During a 4-week pilot study, one exercise session per week was conducted. Simultaneously, interviews, psychometric scales, and functional tests were administered to assess the subjects' conditions and evaluate the study's application methods. Throughout this period, 30-min classes (pre-training, easy-level) were provided to gain insights into the implementation of exercise programs, assess the suitability of the spaces and structures for the classes, and test the participants' rating of perceived exertion.

### Statistical data analysis

2.9

The assumption of normality was assessed using the Kolmogorov-Smirnov test with Lilliefors' significance correction, as well as through visual inspection of normality plots. For the specific case of comparing participants in the MEP intervention programs and comparison with HEP control group individuals, who were measured twice on the same variables at baseline and after 8 weeks of intervention, we will use either an independent T-test or Wilcoxon test, depending on data assumptions. Correlations will be calculated using Spearman's rank correlations.

To determine the effect sizes, the between-subject standard deviation for each dependent variable will be used to convert changes in all variables into standardized Cohen effect sizes (ES). Following Hopkins' guidelines, effect sizes will be categorized as trivial (d ≤ 0.2), small (0.2 < d < 0.6), moderate (0.6 < d < 1.2), large (1.2 < d < 2.0), very large (2.0 < d < 4.0), and nearly perfect (d > 4.0). This will be further confirmed by correlation matrices, where all variables in a group should correlate with at least 50 %, and principal component analyses, where the first component should account for at least 70 % of the variance.

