**Fig. 1 fig1:**
[figure not shown]
**–** Timeline of the EISI study implementation.

A minimum sample size of 20 participants per group will be recruited, which is sufficient to detect significant changes considering a statistical effect size of p = 0.05, as established take into account previous similar study [42]. However, considering a predicted adherence rate of 70 % to the program, a minimum sample size of n = 24 for both the intervention and control groups is justified.

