### Assessments

2.4

This evaluation phase involves initiating contact with the medical staff of the Family Health Strategy (FHS) to acquire pertinent information regarding participants' medical history and current health, factors that may impact their engagement in the exercise programs. To conduct the initial assessments, a standardized data collection instrument was employed. Participants completed this instrument two weeks prior to the program's commencement and one week following its conclusion. The comprehensive data collection instrument comprised eight sections, encompassing: a) socioeconomic and demographic information; b) lifestyle habits; c) physical-functional status; d) health status questionnaire; e) mental well-being and quality of life; f) questionnaire on Covid-19 infections; g) anthropometric measurements; h) fall risk assessment; and i) feasibility and sustainability of interventions. Application of these questionnaires during this phase was carried out by a team consisting of undergraduate and postgraduate students, physical education professionals, and university professors.

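### The unadjusted two-sample test with a single post-programme assessment leaves selective loss uncorrected; assess everyone whatever their attendance and adjust for baseline

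*Protocol article*

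**What the plan says.** Section 2.9 (Statistical data analysis) describes the people compared as MEP and HEP participants "who were measured twice on the same variables at baseline and after 8 weeks of intervention". For that comparison it says "we will use either an independent T-test or Wilcoxon test, depending on data assumptions". It does not say whether the test is applied to post values or to changes. For the effect sizes, the between-subject standard deviation "will be used to convert changes in all variables into standardized Cohen effect sizes (ES"). No baseline adjustment is named.

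Section 2.4 (Assessments) fixes the timing: "Participants completed this instrument two weeks prior to the program's commencement and one week following its conclusion". No intermediate measurement is described.

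The sample-size paragraph in section 2.2 says "A minimum sample size of 20 participants per group will be recruited". It then raises the number "considering a predicted adherence rate of 70 % to the program", so that "a minimum sample size of n = 24 for both the intervention and control groups is justified". Section 2.6.3 (Exercise adherence) computes adherence from sessions attended and uses it as a covariate in a secondary analysis. No rate of loss to the post assessment is stated. Section 2.1 states that allocation is not randomised.

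**The concern.** With two time points and a two-sample test, someone who lacks the second value has neither a post score nor a change score, and the stated test cannot use them. It therefore compares those who came back in one arm with those who came back in the other.

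There is little reason to expect the same kind of loss in both arms. MEP asks for a 50-minute exercise class twice a week. HEP asks for four lectures, a number chosen for the pilot so that people would attend. The introduction itself reports that adherence to exercise programmes declines over time, and links this to age and individual perception, among other barriers.

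Groups are not formed by randomisation, so any selection at follow-up adds to whatever differences exist at entry. An unadjusted test corrects neither. The attendance covariate in the secondary analysis cannot bring back a person with no post value.

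**Working it through.** **1. The plan's own figure.** The inputs are 20 per group and 70 % adherence (section 2.2).

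- If 70 % is read as retention: 20 / 0.70 = 28.6, so 29 per group. The common mistake 20 × 1.30 gives 26. The stated 24 is 20 × 1.20 and is not reproduced.
- With 24 recruited, 20 remain only if loss is at most 1 − 20/24 = 16.7 %.
- If 30 % were lost, 24 × 0.70 = 16.8, about 17 per group, which is below the plan's minimum of 20.
- Standardised difference detectable with 80 % power (t-test, two-sided 0.05 assumed): 0.83 at 24, 0.91 at 20 and 0.99 at 17 per group.

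The 30 % is an assumption here, because 70 % is defined by sessions attended. I use 2, 4 and 7 lost of 24 (8 %, 17 % and 29 %) as the range.

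**2. Formula for the bias.** If a share *d* of MEP is lost and stayers exceed leavers by *g* on some quantity, the stayers' mean exceeds the full-group mean by *d × g*. Random HEP loss adds nothing on average. At *d* = 0.30, *g* = 0.25, 0.5 or 1.0 SD gives 0.075, 0.15 or 0.30 SD. If loss is equally large and equally selective in both arms, the bias is 0.

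**3. Simulation.** Assumptions: no true effect, 24 per arm, pre-post correlation r = 0.7, the same number lost in each arm, HEP loss random. MEP leavers are the people lowest on the driver (baseline, or change) plus random noise of the same SD as the driver. There were 20,000 trials per row. Differences are MEP minus HEP among completers, in SD of the outcome.

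| MEP loss driven by | Lost per arm | Post values | Changes | Baseline-adjusted |
|---|---|---|---|---|
| Low baseline | 2 | +0.08 | -0.03 | 0.00 |
| Low baseline | 4 | +0.14 | -0.06 | 0.00 |
| Low baseline | 7 | +0.24 | -0.10 | 0.00 |
| Little improvement | 2 | +0.04 | +0.09 | +0.07 |
| Little improvement | 4 | +0.08 | +0.16 | +0.13 |
| Little improvement | 7 | +0.13 | +0.26 | +0.22 |

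Repeat runs gave +0.21 to +0.24 for post values at 7 lost under baseline-driven loss, and -0.03 to -0.04 (2 lost) up to -0.10 to -0.11 (7 lost) for changes.

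Hand check at 7 lost:

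- **Baseline-driven loss:** stayers exceed leavers by about 1.14 SD at baseline, so the baseline shift is 7/24 × 1.14 = 0.33. The post shift is 0.7 × 0.33 = +0.23 and the change shift is (0.7 − 1) × 0.33 = -0.10. Both agree with the table.
- **Change-driven loss:** the gap in change is about 0.88 SD, and 7/24 × 0.88 = +0.26.

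False-positive rates at 7 lost (nominal 5 %) are 11 % for post values under baseline-driven loss and 18 % for changes under change-driven loss. For changes under baseline-driven loss the rate is about 6 %, close to nominal. Analysing everyone gives about 0 in both scenarios.

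**The case against.** Four points on the other side have force.

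- **The phrase is not an exclusion rule.** A reader might infer that section 2.9 restricts the analysis set to completers. The clause reads more naturally as a description of the pre-post design. That objection stands. The consequence comes from the named test and the single post assessment, not from the clause.
- **30 % is not the plan's dropout figure.** A reader might infer it from the 70 %, since section 2.2 uses that number to raise the sample size as an attrition allowance would. But section 2.6.3 defines adherence by sessions attended. A poor attender can still be assessed, and a good attender can miss the assessment. So 30 % is neither a stated rate nor an upper bound. Using attendance as a covariate also suggests that low attenders are meant to stay in.
- **The bias need not favour MEP.** It is tempting to say that the loss pushes towards the study hypothesis. It does so for post values, and for changes if non-improvers leave. If people with low baseline values leave, the change contrast goes against MEP. The larger figures also need strong selection: a gap of nearly 0.9 SD in change between stayers and leavers, with purely random HEP loss.
- **Silence is not the fault.** Analysis sets and missing-data handling are commonly left to a full protocol or SAP, which is not shown. Their absence from a condensed article is no finding.

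What survives is narrower. The article does fix a method, that method is unadjusted, and it has no use for a person with one measurement.

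**Conclusion.** The point holds as a weakness of the stated method. It is worth correcting, but it does not show that the results will be biased. Under the assumptions given (no true effect, r = 0.7, random HEP loss, 2 to 7 of 24 lost per arm), the completers' comparison can move by under 0.1 SD at light loss and by roughly a quarter of an SD at the heaviest loss considered. On the effect-size scale in section 2.9, the latter is enough to label a true zero as small (above 0.2). With equal and equally selective loss in both arms, the bias vanishes.

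Baseline adjustment removes the baseline-driven part entirely, but it leaves +0.22 of +0.26 SD when non-improvers leave. Only measuring the leavers deals with that case.

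**What to change.** - **Section 2.4:** state that every enrolled participant is invited to the post assessment at the planned time, whatever their attendance, and is analysed in the group they entered. This is the main remedy.
- **Section 2.9:** replace the unadjusted test by a model of the post value with group and the baseline value as terms.
- **Back-up:** add one sensitivity analysis in which MEP participants without a post value are assumed not to have improved, and report losses by arm.

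The cost is about one sentence in each section, some extra contact with leavers through the Family Health Units already involved, and a little more analysis. The estimates may turn out less favourable to MEP.

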## Abstract

The EISI study protocol aims to address the low participation rate in physical exercise programs among older individuals, emphasizing its significance as a non-pharmacological therapeutic approach for overall health and increased physical activity. The objectives include implementing physical activity (PA) and educational health programs in Jequié, Bahia, Brazil, targeting the Family Health Strategy population to enhance local physical activity levels among older individuals. The study also seeks to evaluate the program's feasibility, safety, and sustainability for large-scale implementation, along with assessing its impact on immune and inflammatory response biomarkers to the SARS-CoV virus, as well as physical-functional and brain health. Participants, aged 60 or above, will be divided into two groups: multicomponent exercise (MCE) and behavioral change interventions (BCI). The study employs a mixed-method approach, utilizing a non-randomized controlled short-term pathway model for a 4–8 weeks of pilot study and 16-week intervention impact assessment. Data collection encompasses various aspects such as sociodemographic information, mental health, physical fitness, fall risk, functional capacity, anthropometric measurements, hemodynamic assessment, habitual physical activity, and health-related quality of life. Blood and saliva samples are collected for cytokine and antibody biomarker analysis related to SARS-CoV immunity. Pre- and post-intervention evaluations for both groups will be conducted, with the hypothesis that MCE will yield more favorable responses compared to BCI. The study's holistic approach, including the assessment of feasibility, safety, and sustainability, aims to contribute to achieving Sustainable Development Goals (SDG) 3 and SDG 9 b y promoting accessible and sustainable healthcare initiatives for older individuals. This research aligns with global efforts to enhance health and well-being, emphasizing the importance of regular exercise in the aging population.

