### Study design

2.1

The EISI-SP will be a community intervention study, using a non-randomized controlled (nRCT), and short-term pathway model lasting 8–10 weeks [37], with two arms comprised physical exercise group versus control group with lifestyle behavioral change intervention. A pre- and post-design will be employed to assess the impact of the EISI program on several physical, metabolic, cognitive, and immunological function variables in the quantitative analysis. Additionally, a mix method of qualitative-quantitative approach will be conducted to evaluate the components of the RE-AIM model. This study protocol was developed based on the SPIRIT guidelines too [38].

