#### Exercise adherence

2.6.3

Exercise adherence to the intervention protocol will be carefully monitored by the instructors. The levels of adherence for both the HEP and MEP groups will be calculated based on the number of attended sessions, which will be used as a co-variable in secondary analysis of the exercise outcomes. In case of an absence from two consecutive classes, the instructors and research team staff will proactively motivate and encourage the participants to maintain their attendance. It is expected that either the MEP group or the HEP control group attend sessions with a frequency of less than 70 % in both intervention programs.

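### The non-randomised pre-post comparison is tested only with an unadjusted t-test or Wilcoxon test: the tested quantity is not stated and no baseline value or confounder is adjusted for

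*Protocol article*

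**What the plan says.** Section 2.1 (Study design) describes the trial as "using a non-randomized controlled (nRCT), and short-term pathway model lasting 8–10 weeks", with two arms. It adds: "A pre- and post-design will be employed to assess the impact of the EISI program". The Abstract says that participants "will be divided into two groups: multicomponent exercise (MCE) and behavioral change interventions (BCI", and states the hypothesis that exercise will give the better responses. I found no allocation rule, matching or stratification.

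Section 2.9 (Statistical data analysis) describes the people in the MEP versus HEP comparison as those "who were measured twice on the same variables at baseline and after 8 weeks of intervention", and for that comparison says "we will use either an independent T-test or Wilcoxon test, depending on data assumptions". The rest of the section covers normality checks, Spearman correlations, effect sizes and principal components. On effect sizes it says that "the between-subject standard deviation for each dependent variable will be used to convert changes in all variables into standardized Cohen effect sizes (ES".

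The only covariate named in the article is session attendance, in Section 2.6.3 (Exercise adherence): "which will be used as a co-variable in secondary analysis of the exercise outcomes".

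**The concern.** In a non-randomised comparison the groups can be expected to differ at baseline, on the outcome itself and on prognostic factors. Neither named test takes a covariate, so nothing in the stated analysis deals with that. Attendance is measured after baseline and enters only a secondary analysis, so it cannot correct a baseline difference.

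The sentence also leaves open what is tested. A test on post values carries a baseline gap into the estimate. A test on changes removes a constant gap but leaves regression to the mean and confounding by other characteristics. The two versions can err in opposite directions, so a reader cannot tell which bias the result would carry.

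At stake is the test of the study's effectiveness hypothesis, since the same sentence covers every quantitative outcome.

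**Working it through.** The plan gives no figure on this point to reproduce, so the check asks how far the stated test can be wrong when exercise has no effect.

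**Inputs.** From the article: a minimum of 20 per group and a 0.05 level (Section 2.2), and two measurements per person (Section 2.9). Assumed: two-sided testing, SD 1 within each group at both visits, baseline imbalance δ = 0.3 to 0.5 SD, pre-post correlation ρ = 0.6 to 0.8.

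**Case A: both groups regress to a common mean.**
- Post-value t-test: bias = ρδ; standard error = √(2/20) = 0.316; 38 degrees of freedom.
- Change-score t-test: bias = −(1−ρ)δ, against the group that starts higher; SD of change = √(2(1−ρ)), which is 0.894 at ρ = 0.6 and 0.632 at ρ = 0.8; standard error = that SD × 0.316.
- Type I error comes from the noncentral t distribution with noncentrality = bias / standard error. Example: 0.8 × 0.5 = 0.40, and 0.40 / 0.316 = 1.265, which gives 23.4 %.

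| ρ | δ | Post-value bias | Type I error | Change-score bias | Type I error |
|---|---|---|---|---|---|
| 0.6 | 0.3 | 0.18 | 8.6 % | −0.12 | 7.0 % |
| 0.6 | 0.5 | 0.30 | 15.2 % | −0.20 | 10.6 % |
| 0.8 | 0.3 | 0.24 | 11.5 % | −0.06 | 6.0 % |
| 0.8 | 0.5 | 0.40 | 23.4 % | −0.10 | 7.8 % |

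In simulations of this case (ρ 0.5-0.8, imbalance up to 0.8 SD), ANCOVA on the baseline value had bias of about 0 and type I error of 0.046-0.051.

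**Case B: the group gap would simply persist.**
- Change-score t-test: bias 0, type I error about 5 %.
- Post-value t-test: bias = δ, that is 0.30 to 0.50 SD. The noncentrality is 0.30/0.316 = 0.949 to 0.50/0.316 = 1.581, and type I error is 15 % to 34 %.
- ANCOVA on the outcome's baseline alone: bias = (1−ρ)δ, from 0.2 × 0.3 = 0.06 to 0.4 × 0.5 = 0.20 SD. The standard error is about √(1−ρ²) × √(2/20 + δ²/38) with 37 degrees of freedom. For ρ = 0.6, δ = 0.5 it is 0.8 × 0.3265 = 0.261, the noncentrality is 0.766, and type I error is about 12 %. For ρ = 0.8, δ = 0.3 it is 0.192, the noncentrality is 0.313, and type I error is about 6 %.

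**Precision.** The residual variance of ANCOVA relative to a change-score test is (1−ρ²)/(2(1−ρ)) = (1+ρ)/2, which is 0.80 at ρ = 0.6 and 0.90 at ρ = 0.8. The gain is 10-20 % before the cost of further covariates.

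**The case against.** The strongest reply is that the plan may well mean change scores. Section 2.1 speaks of a pre-post design, Section 2.9 stresses that the same variables were measured twice, and the effect sizes are built on changes. On that reading the baseline level gap cancels and the remaining bias is the smaller one, in the opposite direction. This stands as far as it goes. The post-value figures must not be presented as what the trial will suffer, because the article does not say that post values are compared. But the article does not say changes either, and a change-score test still leaves regression to the mean and other confounders.

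A second reply is that ANCOVA is no cure. In Case B it is biased by about as much as the change score is in Case A. This is correct. It means that baseline adjustment needs prognostic covariates and a change-score check beside it. It does not rescue a plan with no adjustment at all.

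A third is that a condensed article leaves covariate lists to the analysis plan, and that Section 2.6.2 calls the work a pilot. But the article is not silent here: it names the method, and the method does not fit the design.

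Two stronger readings should be resisted. A reader might infer that participants chose their own group; the article says only that they are divided without randomisation. A reader might also infer that a failed normality check switches from a between-group test to a within-group signed-rank test. Beside an independent t-test, in a sentence comparing two groups, rank-sum is the natural reading, and naming it settles the matter.

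**Conclusion.** The concern holds in this form: the only stated test of MEP against HEP is unadjusted, its target (post value or change) is unspecified, and the baseline data that could reduce confounding are collected but not used. Under the Case A assumptions the bias is 0.18-0.40 SD (type I error about 9-23 %) if post values are tested, and 0.06-0.20 SD against the group that starts higher (about 6-11 %) if changes are tested.

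The mismatch between design and test is certain from the text. The size is not: imbalance and correlation are assumptions, and the direction depends on a choice that the article does not state. It would go too far to say that baseline differences will be read as the exercise effect, because a persistent gap cancels out of a change score.

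**What to change.** - Make the between-group analysis of each outcome a linear model of the post value on group, baseline value and a short pre-specified set of baseline covariates already collected, such as age, sex and education in few categories. Report the adjusted difference with its 95 % CI.
- For skewed outcomes (cytokines, antibodies, activity minutes), log-transform or use robust or bootstrap standard errors.
- Add a change-score analysis with the same covariates as a sensitivity check, given the bias that ANCOVA leaves when a gap persists.
- If a Wilcoxon test is kept, call it the rank-sum test and say which quantity it is applied to.
- Do not adjust the main analysis for infection or booster doses between visits. These occur after baseline, and infection could be affected by an intervention studied for its immune effects. Report them by group or in a sensitivity analysis.
- State how participants reach each group, and that residual confounding remains.

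The cost is analysis wording. The covariates named above are already planned; only booster dates would be new. The downside is a few degrees of freedom and a linear-model assumption at about 40 participants, so the covariate list must stay short. The variance gain over a change-score test is at most 10-20 %, so the case for the change rests on bias more than on precision.

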#### Socioeconomic and demographic information

2.4.1

The following demographic and personal information based on will be collected [43]: gender (male/female), age (continuous variable in complete years), marital status (married, cohabiting, single, divorced/separated, widowed), education level (never attended school, reads and writes their name, primary school: 1st to 4th grade, lower secondary school: 5th to 8th grade, high school: 1st to 3rd year, higher education: completed, incomplete, 3rd to 4th year), race/ethnicity (white, yellow (oriental), mixed race, indigenous origin, black, unknown), number of living children (variable in Arabic numerals), housing characteristics (living with others, living alone, no response, unknown), religion (Catholic, Protestant, Jewish, Spiritus/Kardecist, Umbanda, Other), average per capita family income (quantified in Brazilian Reais R$, *2022: minimum wage R$ 1302.00), and occupation (yes or no).

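### Section 2.9 fixes an unadjusted two-sample test as the only MEP-HEP comparison in a non-randomised study, and does not say whether it compares final values or changes

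*Protocol article*

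**What the plan says.** Section 2.1 describes a two-arm pre-post study "using a non-randomized controlled (nRCT"). The article describes no matching or stratification.

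Section 2.9 gives the one between-arm analysis. For participants "who were measured twice on the same variables at baseline and after 8 weeks of intervention", it says "we will use either an independent T-test or Wilcoxon test, depending on data assumptions". No covariate is named. The next paragraph says the between-subject SD "will be used to convert changes in all variables into standardized Cohen effect sizes (ES"), but the sentence naming the test does not say whether changes or final values are tested.

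Section 2.4.1 records sex and "age (continuous variable in complete years"), along with education and income. The only covariate mentioned for any analysis is session attendance in section 2.6.3, "which will be used as a co-variable in secondary analysis of the exercise outcomes". Attendance is measured after the programme starts, so it cannot correct a difference present at the start.

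On size, section 2.2 (below Fig. 1) says "A minimum sample size of 20 participants per group will be recruited", and then that "a minimum sample size of n = 24 for both the intervention and control groups is justified".

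**The concern.** Without randomisation, nothing makes the two arms alike at the start, in the outcome itself or in age and sex. An unadjusted two-sample test can turn such a difference into an apparent programme effect, in either direction. The hypothesis that exercise does better than education rests on this test.

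The outcome is also measured at baseline. If the test uses only final values, that measurement is left out and the standard error is larger than it need be in a study of 20 to 24 per group.

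This is not a detail left for a later document. Section 2.9 commits to a specific unadjusted test, and an analysis plan that followed it would inherit the problem.

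**Working it through.** **Inputs from the article.** Non-randomised arms (2.1); one baseline and one post-programme measurement (2.9); n = 20 per group as the minimum, 24 as the raised figure (2.2). The article gives no figure for precision or bias on this point. The 20 cannot be re-derived, because no standardised difference, SD or power is stated, so it is taken as given.

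**Assumptions, not in the article.** Pre-post correlation r = 0.5, 0.7 or 0.8; baseline gap g = 0.5 SD; equal SDs at both times; normal data; no true effect. Units are SDs of the outcome.

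**Step 1: standard errors at n = 20 per group.** The base is √(2/20) = 0.316. The variance factor is 1 for final values, 2(1 − r) for changes and 1 − r² for baseline-adjusted regression (ANCOVA).

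| r | Final values | Changes | ANCOVA |
|---|---|---|---|
| 0.5 | 0.316 | 0.316 | 0.274 |
| 0.7 | 0.316 | 0.245 | 0.226 |
| 0.8 | 0.316 | 0.200 | 0.190 |

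A two-sided 5 % t-test on final values with 20 per group has 80 % power for 0.909 SD. At r = 0.7 this becomes 0.909 × √0.6 = 0.70 SD for changes and 0.909 × √0.51 = 0.65 SD for ANCOVA. With 24 per group every standard error is multiplied by √(20/24) = 0.91, and the biases below do not change.

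**Step 2: bias if both arms regress to a common mean.** Without treatment the gap shrinks from g to r·g. Final values then carry r·g, changes carry r·g − g = −(1 − r)·g, and ANCOVA carries r·g − r·g = 0. False-positive rates are from simulation with n = 20 per group.

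| r | Final values: bias, false positives | Changes: bias, false positives | ANCOVA: bias, false positives |
|---|---|---|---|
| 0.5 | +0.25, 12 % | −0.25, 12 % | 0, 5 % |
| 0.7 | +0.35, 19 % | −0.15, 9 % | 0, 5 % |
| 0.8 | +0.40, 23 % | −0.10, 8 % | 0, 5 % |

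**Step 3: bias if the arms are stably different groups.** Each arm regresses to its own mean and the gap stays at g. Final values then carry the whole gap, 0.50 SD. Changes carry g − g = 0, with false positives of about 5 %. ANCOVA carries g − r·g = (1 − r)·g, which is +0.25 / +0.15 / +0.10 SD at r = 0.5 / 0.7 / 0.8, with false positives of about 13 / 10 / 8 %.

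**Step 4: what the two models have in common.** Final values are biased under both. Changes and ANCOVA are each unbiased under one model and biased under the other, by the same amount (1 − r)·g with opposite sign. The article does not say how the arms are formed, so it does not settle which model applies. None of the three, as computed here, deals with age, sex or other measured differences.

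The figures are for the t-test. The rank test is equally unadjusted.

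**The case against.** **The test may be meant for changes.** Section 2.9 stresses two measurements per person and expresses effect sizes as changes, so this reading is at least as natural. The baseline measurement is then used, and the loss against ANCOVA at r = 0.7 is only 0.245 against 0.226. This stands. A reader might infer that the plan throws away precision outright, with the detectable effect falling from 0.91 to 0.65 SD on adjustment; that holds only for final values. For changes it falls from 0.70 to 0.65 SD.

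**ANCOVA is not unbiased in general.** This also stands. A reader might infer that baseline adjustment removes the bias and brings false positives back to 5 %. Step 3 shows that this depends on the arms regressing to a common mean, which the article gives no ground to assume in a non-randomised study. Equally, regression to the mean in a change-score analysis is a possibility here, not a fact.

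**A baseline gap need not pass into the result.** A reader might infer that any gap goes in whole. How much enters depends on the reading and the model: r·g or all of it for final values, and −(1 − r)·g or nothing for changes. The gap and r are both assumed. Chance imbalance is no guide to the gap either: a random split of 20 per group exceeds 0.5 SD in about 11 % of cases, but that describes randomised allocation.

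**A condensed article may leave covariates to the full plan.** A missing covariate list would indeed be no finding. The point here is the unadjusted test that is named as the between-arm analysis.

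**Conclusion.** The point holds in a limited form and should be fixed; it does not rank as a must-fix. The stated MEP-HEP comparison makes no adjustment for any measured confounder in a non-randomised study, and it does not define the quantity compared.

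If final values are meant, the result is biased under both models considered: for a 0.5 SD gap and r of 0.5 to 0.8, by about 0.25 to 0.40 SD with regression to a common mean, and by more if the arms are stably different. The standard error at r = 0.7 is about 1.4 times the adjusted one (0.316/0.226). If changes are meant, the precision loss is small (0.245/0.226, about 8 %), and bias of −(1 − r) times the gap arises only under a common mean.

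These sizes rest on assumed values of r and of the gap. The direction of the advice does not: baseline values, age and sex are already collected, and using them addresses differences that the stated test ignores.

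**What to change.** In section 2.9:

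- Make the between-arm analysis a linear regression of the post-programme value on arm, with the baseline value of the same outcome, age and sex as covariates. Use robust standard errors, or ranks where the residuals are badly skewed. Report the adjusted MEP minus HEP difference with its 95 % confidence interval.
- Add a change-score analysis adjusted for age and sex as a stated sensitivity analysis. Say why: allocation is not random, and the two methods rest on different assumptions about how the arms would have moved without treatment. If they disagree, report both.
- Keep the t-test or Wilcoxon test as an unadjusted supporting result only, and state whether it is applied to final values or to changes.

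The cost is wording and a few lines of code, with no new data. The covariates use a few degrees of freedom, which about 40 participants can bear if the list stays short. Unmeasured confounding remains and should be stated as a limitation.
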